## Protocol

**Aim:** To determine a standard specimen collection and testing method for measuring azithromycin concentrations in cervical cellular material in women following a single 1 gram dose.

### Rationale:

- There is considerable concern internationally about chlamydia treatment failure.
- Studies have found that chlamydia treatment failure may be at least 8%, considerably higher than the 2-3% failure expected based on results of previous chlamydia treatment trials that with the exception of one trial, all used the less sensitive culture method to measure antimicrobial cure.
- A treatment failure rate of 8% rather than 2-3% means a further nearly 3,000^11 in Australia and 70,000^12 women in the USA were inadequately treated for chlamydia in 2009, leading to longer duration of infection, increased risk of developing sequelae and continued transmission.
- **It remains uncertain if this treatment failure is because of (1) re-infection by an untreated partner; (2) failure of the drug itself due to poor absorption from the stomach or low concentrations in female genital tissue where it is needed to work, or; (3) the body's immune system's inability to fight the infection.**
- We have received NHMRC funding to conduct a large cohort study of 450 women that aims to estimate azithromycin treatment failure for genital chlamydia infection. In order to understand failure due to reason (2) above (poor absorption), we propose to develop a test to measure the concentration of the drug in female cervical cellular material. We wish to determine whether azithromycin is present at the cervix in sufficient concentrations to treat chlamydia. This was done by Worm and colleagues in the early 1990s on mucus aspirated from the cervix, a method unlikely to be acceptable to women today as part of a large cohort study.
- **The purpose of this study is to develop a test and specimen collection method that measures azithromycin absorption in cervical cellular material (mucus and cells) using a specimen collection method that is practical and acceptable to women – vaginal swabs or tampons.**

### Background:

#### Chlamydia rates continue to increase

Worldwide, chlamydia diagnosis rates have increased dramatically over the last decade – it is the most commonly diagnosed bacterial STI throughout the developed world. Chlamydia diagnosis rates have increased by over 400% in the last decade in Australia with 72,123 cases diagnosed in 2010. Part of this increase reflects increased testing - the more you test, the more you diagnose. Testing rates have increased from 1% in 2000 to 3.5 % in 2010^14 and current trends suggest over 100,000 cases will be diagnosed annually within 5 years. Analyses of sentinel clinic data show that the prevalence of infection in the population is increasing at a rate of 12% per year. Chlamydia can have considerable adverse health consequences particularly for women: up to two thirds of tubal factor infertility and one third of ectopic pregnancy may be due to past infection. This highlights that the burden of chlamydia will continue to increase in Australia.

#### Repeat chlamydia infections are very common and drive chlamydia transmission

Repeat chlamydia infections are common following treatment and account for a substantial proportion of incident infections. Several studies have reported alarmingly high chlamydia repeat infection rates among young women tested again post treatment. An Australian cohort of 1116

---

 Worm et al. Genitourin Med 1995; 71:244-246

young women found that among those women testing positive at recruitment, 18% tested positive again at 3 months (95%CI:8%, 34%) following treatment. In the UK, a prospective cohort of 16 to 24 year old women from general practice reported a repeat infection rate of 29.9% per year after treatment (95% CI: 19.7, 45.4). Another cohort of adolescent women in the US reported a repeat infection rate of 34% per year. Although re-testing at 3 months after a positive diagnosis is recommended in Australia, re-testing rates remain low. A recent analysis of surveillance data found that only 14% are retested within 4 months following a positive diagnosis. This suggests that there are many more repeat infections that go undetected in the population, leading to further transmission. **If we genuinely want to better control this chlamydia, then we need to better understand whether these are true re-infections or treatment failures so that we can further enhance partner notification or change treatment regimens.**

#### Repeat infections may represent treatment failure

Repeat infections may represent: 1) re-infection due to unprotected sexual contact with an infected partner; 2) treatment failure as a result of noncompliance with treatment, poor absorption of the drug, reduced antimicrobial susceptibility or antimicrobial resistance; or 3) persistence due to host factors such as immune response or other undefined host factors.

While most repeat infections are generally considered to be re-infections through exposure to an infected partner, emerging evidence suggests that treatment failure may account for a significant proportion. A partner treatment study found that among female participants who reported no sexual intercourse after treatment, 22 of 289 (8%; 95%CI: 5%, 11%) had persistent infection at follow up, suggestive of treatment failure. A cohort of adolescent females also found a treatment failure rate of 7.9% (95%CI: 4%, 10.1%). There is also in vitro evidence that chlamydia can enter a persistent form where infected cells exposed to  $\beta$ -lactam antibiotics, interferon- $\gamma$  or deprived of iron supplements or amino acids can exhibit persistence. This allows chlamydia to remain dormant, non-infectious and undetectable by culture but, on removing the stressful conditions, it can be recovered by culture. There is also evidence that latent infection may not be detectable, even using PCR, if only cells shed from the mucosal surface are sampled. It is not known how often this persistent state persists in vivo and whether removal of treatment can trigger reactivation.

#### Distinguishing between treatment failure and re-infection is vital for chlamydia control

Distinguishing between treatment failure and re-infection is important to focus treatment recommendations and infection control mechanisms. For example, if many repeat infections are due to antibiotic treatment failure, then international recommendations on chlamydia treatment need to be re-evaluated. If most are re-infections, then strategies to expedite partner treatment are necessary. Treatment failure will lead to persistent infection and if left untreated, chlamydia infection can last for several years. This increases a woman's risk of developing further chlamydia sequelae and contributes to continued transmission in the population.

#### There are concerns about the evidence supporting current chlamydia treatment regimens

The recommended first line treatment for uncomplicated genital chlamydia infection in Australia is a 1gram dose of the macrolide antibiotic, azithromycin. While doxycycline 100mg twice daily for 7 days is a second line treatment for uncomplicated chlamydia in Australia, it is not widely used because there are concerns about compliance given the longer duration of treatment. A meta-analysis of chlamydia treatment reported a 97% cure rate for azithromycin and 98% for doxycycline. However, of the 12 trials included in this meta-analysis, 11 used culture or immunoassay rather than the more sensitive PCR to determine microbial cure at study end and

one third had significant attrition rates of at least 25%. Further, three of the studies included in the meta-analysis had cure rates of 81-92% for azithromycin compared with 99-100% for doxycycline. Given the use of culture rather than PCR, it is likely that the treatment efficacies in the treatment trials were over-estimated.

## **Research methodology**

### Sampling frame

Women aged 18 years or older recruited via word of mouth, advertising on the University of Melbourne Staff News email or as patients attending at Melbourne Sexual Health Centre (MSHC, Victoria)

We aim to recruit 12-20 women.

### Inclusion criteria

- Women aged 18 years and older
- Must have adequate English and comprehension skills to give informed consent.
- Able to attend the clinic at regular intervals during the study to collect and drop of specimens.

### Exclusion criteria

- Pregnant women
- Women currently menstruating
- Women on medication likely to significantly interact with Azithromycin eg. Cyclosporin, digoxin
- Women known to have any allergies associated with macrolides (very rare).

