### Recruitment

Interested women and eligible women attending MSHC as a patient will be seen by the research assistant. The study will be advertised in the Staff News email at the University of Melbourne and by clinical staff at MSHC.

The research assistant will explain the study to them, assess for eligibility and take informed consent. The research assistant will explain how to collect specimens for investigation and will take a blood specimen.

A small number of women who have tested positive for chlamydia will also be recruited when they return to the clinic for treatment.

All participants will be given a 1 gram stat dose of azithromycin to take at recruitment regardless of whether or not they test positive for chlamydia. Please note: azithromycin is a very well tolerated and relatively benign antibiotic. It is recommended by the World Health Organisation for the 'presumptive' treatment of STIs for over a decade now (2) Azithromycin has also been available without a prescription in the UK since 2008 and is also given to sexual partners regardless of whether or not they have chlamydia diagnosed and (3) has negligible, clinically significant drug interactions and minimal/mild side effects. It is also regularly given to patients

---

 World Health Organisation, 2008 - Periodic presumptive treatment for sexually transmitted infections. Experience from the field and recommendations for research. *Presumptive is defined as a one-time treatment for a presumed infection in a person, or a group of people, at high risk of infection*

 <http://www.mhra.gov.uk/NewsCentre/Pressreleases/CON023105>

 Rapp R. Pharmacokinetics and Pharmacodynamics of Intravenous and Oral Azithromycin: Enhanced Tissue Activity and Minimal Drug Interactions. *Ann Pharmacother* 1998;32:785-93.

who have contact with chlamydia regardless of whether or not they are diagnosed with the infection. Additionally the USA FDA has recently approved the labelling of Zithromax with the indication that ***“Therapy with ZITHROMAX may be initiated before results of these tests are known”***.

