**Questionnaire:**

- 1) What is your age?
- 2) What is your height?
- 3) What is your weight?
- 4) Please list any medications you are currently taking, including any contraceptive medication
- 5) Are you using any vaginal lubricants or other gels?

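### Recent azithromycin use is neither excluded nor reliably captured, and no specimen is fixed as pre-dose, so a measured concentration cannot be firmly attributed to the study dose

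*Protocol*

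**What the plan says.** **Who is recruited.** Sampling frame in the Protocol sets the target ("We aim to recruit 12-20 women") and draws on word of mouth, a university staff email and clinic patients ("or as patients attending at Melbourne Sexual Health Centre"). Recruitment adds a small number of women who have tested positive for chlamydia and are returning for treatment.

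**Who is excluded.** There are four exclusions: pregnancy, current menstruation, interacting drugs ("Women on medication likely to significantly interact with Azithromycin eg. Cyclosporin, digoxin") and macrolide allergy ("Women known to have any allergies associated with macrolides (very rare"). Neither this list nor Inclusion criteria mentions earlier azithromycin or other macrolide use.

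**What is asked.** Data collection plans to record medications without giving a look-back period. The question put to the woman is about present use: "Please list any medications you are currently taking, including any contraceptive medication".

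**When specimens are taken.** The dose is given at enrolment: "All participants will be given a 1 gram stat dose of azithromycin to take at recruitment". Recruitment mentions the blood specimen before it mentions the dose, and Follow up ties the first swab and the blood to enrolment. Neither says whether they precede the dose. The advertisement has women take the drug first and collect swabs afterwards, and it refers to one blood specimen. Analysis describes concentration over time for each participant and mentions no baseline value.

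**The concern.** The aim is a collection and testing method for concentrations after a single 1 g dose. That requires the measured drug to come from that dose, and the measured signal to be drug at all. The protocol as written secures neither.

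- A woman who finished a single dose of azithromycin a week earlier is eligible, and she can truthfully leave it out when asked what she is taking now.
- Without a pre-dose specimen there is nothing to show that residual drug was present.
- The same missing specimen would have served as a per-woman check on background signal. This matters even if no recent user enrols, because the assay is being developed on vaginal swab and tampon material and the study itself records lubricants and gels.

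Eligibility, the questionnaire and the order of dose and specimen are protocol matters. A blank that was never collected cannot be recovered by any later analysis plan.

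**Working it through.** **No stated figure to reproduce.** The only design number is the target of 12 to 20 women, given without inputs. The protocol gives no half-life and no frequency of recent use. Both are assumed below.

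**1. Carry-over in one woman.** Assume first-order decline with half-life h days, linear superposition, and an equal dose taken d days before the study dose. In the declining phase, at time t after the study dose:

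C(t) = A × 2^(−t/h) + A × 2^(−(t+d)/h) = A × 2^(−t/h) × [1 + 2^(−d/h)]

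The relative inflation is therefore 2^(−d/h):

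| Earlier dose | h = 2 days | h = 4 days |
|---|---|---|
| d = 7 | 2^(−3.5) = 8.8% | 2^(−1.75) = 29.7% |
| d = 14 | 2^(−7) = 0.8% | 2^(−3.5) = 8.8% |
| d = 28 | 2^(−14) = 0.006% | 2^(−7) = 0.8% |

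With a wider assumed range of 1 to 5 days, the inflation is 0.8% to 37.9% at 7 days, 0.01% to 14.4% at 14 days, and 0% to 2.1% at 28 days.

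**2. Level or slope.** The bracket in the formula does not contain t. The earlier dose multiplies the whole declining phase by a constant, so on the log scale the line moves up and its slope is unchanged.

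**3. Effect on a group mean.** If k of n women are affected and all have equal underlying levels, the mean rises by (k/n) × inflation. For a dose 7 days earlier:

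- h = 4, two of 12: (2/12) × 29.7% = 5.0%
- h = 4, one of 12: (1/12) × 29.7% = 2.5%
- h = 4, one of 20: (1/20) × 29.7% = 1.5%
- h = 2, two of 12: (2/12) × 8.8% = 1.5%
- h = 2, one of 20: (1/20) × 8.8% = 0.4%

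**4. Chance that it happens.** If a fraction p of recruits has recent use, the chance of at least one such woman is 1 − (1 − p)^n:

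| Assumed p | n = 12 | n = 20 |
|---|---|---|
| 2% | 21.5% | 33.2% |
| 5% | 46.0% | 64.2% |
| 10% | 71.8% | 87.8% |

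**5. Order of dose and specimen.** Recruitment and Follow up are compatible with either order. The advertisement is the only place that states one, and it puts the swabs after the dose. On the text as it stands, a pre-dose swab is not guaranteed and may be ruled out.

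**The case against.** The strongest case against has four parts.

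- **The exposure may be rare.** Part of the recruitment is through word of mouth and staff email. Chlamydia-positive women join when they return for treatment, so before that diagnosis is treated. A clinic prescriber is involved in every dose, and Data collection is worded more broadly than the questionnaire. All of this lowers the risk, but none of it is a washout or a look-back question.
- **The protocol does not say the drug is commonly given to these recruits.** A reader might infer from Recruitment ("It is also regularly given to patients" who have had contact with chlamydia) that it is regularly dispensed at this clinic. The sentence names no place and belongs to an argument about tolerability. It makes earlier exposure plausible and no more.
- **The numerical effect is modest.** A reader might infer that one or two affected women would visibly shift the mean curve and distort the elimination estimate. The documents do not support this. Analysis names neither quantity, the mean moves by at most about 5% in the cases worked above, and under first-order superposition the slope does not change.
- **The aim is a collection method, not a pharmacokinetic estimate.** An offset in one or two women may not alter whether swabs or tampons are workable. That is fair, but a testing method still needs a blank, and the plan does not provide for one.

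What stands of the objection is that the harm is conditional and probably small on average. It does not remove the gap.

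**Conclusion.** The point holds as a cheap improvement. Recent azithromycin use is not excluded and not reliably captured, and no specimen is fixed as pre-dose. If a woman with residual drug enrols, or if the swab material gives background signal, her values cannot be attributed to the study dose. The main harm is an individual curve whose error cannot be recognised, rather than a biased group result.

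The size is about 9% to 30% on that woman's declining phase for an equal dose 7 days earlier, and about 1% to 9% for one 14 days earlier. This rests on assumed half-lives of 2 to 4 days, a single first-order decline and equal doses. The calculation does not cover the early specimens taken while the study dose is still rising. It would be wrong to conclude that residual drug will be counted as absorption: that requires a recent user to enrol, and the documents give no frequency for it.

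**What to change.** 1. State in Specimen collection that the first swab at enrolment is collected before the dose and used as that woman's blank.
2. Add a question on use of azithromycin or any other macrolide over a stated look-back period. Four weeks is one example and depends on the assumed half-life: under 1% remains at 28 days for half-lives of 2 to 4 days, but about 2% at 5 days.
3. For this measurement study only, either exclude women with such use or flag them and report them separately. Do the same for any woman whose blank shows drug.
4. Align the advertisement, which now places all swabs after the dose.
5. Acknowledge two limits. A swab blank does not cover the tampon matrix where tampons are used. The single blood specimen cannot be both baseline and post-dose, so the protocol should say which it is.

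**Cost.** One question, one eligibility line or flag, and a stated order of events, using a first swab that the reimbursement schedule already covers. A few clinic patients may become ineligible or be flagged, and the earliest post-dose swab moves to the next specimen. Clinical treatment is unaffected.

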### Recruitment

Interested women and eligible women attending MSHC as a patient will be seen by the research assistant. The study will be advertised in the Staff News email at the University of Melbourne and by clinical staff at MSHC.

The research assistant will explain the study to them, assess for eligibility and take informed consent. The research assistant will explain how to collect specimens for investigation and will take a blood specimen.

A small number of women who have tested positive for chlamydia will also be recruited when they return to the clinic for treatment.

All participants will be given a 1 gram stat dose of azithromycin to take at recruitment regardless of whether or not they test positive for chlamydia. Please note: azithromycin is a very well tolerated and relatively benign antibiotic. It is recommended by the World Health Organisation for the 'presumptive' treatment of STIs for over a decade now (2) Azithromycin has also been available without a prescription in the UK since 2008 and is also given to sexual partners regardless of whether or not they have chlamydia diagnosed and (3) has negligible, clinically significant drug interactions and minimal/mild side effects. It is also regularly given to patients

---

 World Health Organisation, 2008 - Periodic presumptive treatment for sexually transmitted infections. Experience from the field and recommendations for research. *Presumptive is defined as a one-time treatment for a presumed infection in a person, or a group of people, at high risk of infection*

 <http://www.mhra.gov.uk/NewsCentre/Pressreleases/CON023105>

 Rapp R. Pharmacokinetics and Pharmacodynamics of Intravenous and Oral Azithromycin: Enhanced Tissue Activity and Minimal Drug Interactions. *Ann Pharmacother* 1998;32:785-93.

who have contact with chlamydia regardless of whether or not they are diagnosed with the infection. Additionally the USA FDA has recently approved the labelling of Zithromax with the indication that ***“Therapy with ZITHROMAX may be initiated before results of these tests are known”***.

Azithromycin will be prescribed by a MSHC clinician and administered in consultation with the clinician in accordance with routine clinical care at MSHC. All participants will be asked to monitor adverse events and report them to the research assistant. They will receive a study phone number that they can call should they experience any adverse events. The research assistant will report to a safety and monitoring committee (including a senior sexual health physician from MSHC, the head of research/evaluation at MSHC and the chief investigator of the study). Any adverse events will be managed according to MSHC protocol.

#### Specimen collection

Women will be asked to use self collected swabs and/or tampons to collect high vaginal material. These specimens will be immediately placed in a solution containing methanol and placed at -80C within 4 hours following collection. Women will be asked to return to the clinic at regular time intervals to self collect specimens for up to 9 working days. Some participants will be asked if they would be able to collect specimens at home over the weekend and return them to the research nurse the following Monday. This will be voluntary and only be offered to participants by the research nurse if the participant would be able to do this.

#### Specimen testing

Swabs, tampons and blood will be processed at the laboratory. Azithromycin levels as well as its metabolites will be measured using LCMS (Liquid Chromatographic Mass Spectrometry) at Metabolomics, Bio21, University of Melbourne.

#### Follow up

Participants will be telephoned/sent an sms regularly over the 9 working days to remind them to drop off specimens. Women who voluntarily provide weekend specimens will not be contacted during this time.

Women diagnosed with chlamydia at recruitment, will be re-tested again at 3 months and treated again if chlamydia positive again.

Women will be reimbursed with up to a \$100 voucher (\$20 at enrolment and for first swab and blood; \$10 for the next 5 swabs and \$30 for the final swab at day 7) to cover their transport and time costs during the study.

#### Data collection

Participants will be asked to provide the following data:

Age, height, weight, any medications, use of vaginal lubricant or other gels, contact details.

---

 Zuckerman JM et al. Macrolides, Ketolides, and Glycylcyclines: Azithromycin, Clarithromycin, Telithromycin, Tigecycline. *Infect Dis Clin N Am* 23 (2009) 997–1026. *The most common adverse effects reported with azithromycin were diarrhea (3.6%), nausea (2.6%), abdominal pain (2.5%), and headache or dizziness (1.3%)*

 [http://www.accessdata.fda.gov/drugsatfda\\_docs/label/2011/050693s017.050710s033.050711s031.050784s018.050730s026lbl.pdf](http://www.accessdata.fda.gov/drugsatfda_docs/label/2011/050693s017.050710s033.050711s031.050784s018.050730s026lbl.pdf) (page 10) LABEL APPROVED 28/1/2011

